## Abstract

**Background:**

In the paediatric population, pain and distress associated with burn injuries during wound care procedures remain a constant challenge. Although silver dressings are the gold standard for burn care in Australasia, very few high-level trials have been conducted that compare silver dressings to determine which will provide the best level of care clinically. Therefore, for paediatric patients in particular, identifying silver dressings that are associated with lower levels of pain and rapid wound re-epithelialisation is imperative. This study will determine whether there is a difference in time to re-epithelialisation and pain and distress experienced during wound care procedures among Acticoat™, Acticoat™ combined with Mepitel™ and Mepilex Ag™ dressings for acute, paediatric partial thickness burns.

**Methods/Design:**

Children aged 0 to 15 years with an acute partial thickness (superficial partial to deep partial thickness inclusive) burn injury and a burn total body surface area of ≤10% will be eligible for the trial. Patients will be randomised to one of the three dressing groups: (1) Acticoat™ or (2) Acticoat™ combined with Mepitel™ or (3) Mepilex Ag™. A minimum of 28 participants will be recruited for each treatment group. Primary measures of pain, distress and healing will be repeated at each dressing change until complete wound re-epithelialisation occurs or skin grafting is required. Additional data collected will include infection status at each dressing change, physical function, scar outcome and scar management requirements, cost effectiveness of each dressing and staff perspectives of the dressings.

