### Recruitment

A surgical registrar will be notified of a patient with a burn injury by DEM staff and will then determine the patient’s eligibility according to study criteria. The potential participants and their parents/caregivers will be notified of their eligibility to participate in this study by the registrar. Parents/caregivers will then be asked if a member of the research team can speak to them about the study. Informed caregiver consent and child assent (for children 6 years and above) will be gained by an investigator on the study after a discussion with the child and their caregiver regarding the information in the Patient Information Sheet. Once consent has been gained, the investigator will randomise the patient to one of the three dressing treatment arms. Randomisation will be completed using a computerised random number generator and randomisations will be enclosed in sealed, opaque envelopes by an independent party. All dressings will be carried out by staff experienced in burn dressing application. Baseline measures (pain and behavioural scores from child, nurse and parent, pulse rate and respiratory rate) will be recorded by the primary investigator prior to and after the dressing has been applied. The patient will then present at our burn centre every 3–4 days for subsequent dressing changes. Any analgesia given to the patient will be recorded.

The first 3 days post-burn injury often have the highest risk of toxic shock syndrome, which can be potentially fatal if left untreated [10,18]. While the incidence rate of toxic shock syndrome at our burn centre is extremely low to non-existent, phone calls will be made to each participant by the primary investigator within this period. A set of standardised questions will be used to screen for any toxic shock syndrome symptoms and to assess how the child and their parents or caregivers are managing the dressing, and all responses will be recorded.

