All participants in the study will have their dressings changed every 3–4 days at our burn centre as a standard measure. This protocol will be followed until full re-epithelialisation of the wound occurs or grafting of the wound is required [20]. After full re-epithelialisation occurs, participants will be followed up at 3 months and then 6 months to assess skin appearance and/or the presence of scarring.

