#### Pain

Pain and distress will assessed by obtaining: (1) the participant’s self-report of pain intensity using the Faces Pain Scale-Revised (FPS-R) (if participant is aged 3 years or over) [21]; (2) the parent’s report of the participant’s pain intensity using a Visual Analogue Scale-Pain (VAS-P) (alternatively, if participants are aged 8 years or over they will complete the VAS-P in lieu of the caregiver) [22]; (3) the nurse’s observational rating of the participant’s pain and distress using the Face, Legs, Activity, Cry, Consolability (FLACC) scale [23]; and (4) pulse and respiratory rates of the participant.. All four of these measures will be taken before and after dressing removal and before and after dressing application. Pulse and respiratory rates will be recorded once at each time point to provide an objective measure of pain and distress in participants, as increases in these physiological measures have been shown to be indicative of pain and distress [6,24] Any analgesic and/or sedative medication administered to the participant at each dressing change will also be recorded.

Face scales are particularly useful for obtaining self-report pain scores from younger children as they have been reported to be easier to follow than other types of self-report scales and are well-validated measures [25]. The FPS-R is clinically valid for a paediatric population and was chosen over other faces pain scales because of its psychometrically sound characteristics including the exclusion of smiling faces or tears, thus eliminating the possible confusion of pain intensity and affect by children [21]. The VAS-P is a valid and reliable self-report measure of acute pain in children over the age of 8 years [22]. The VAS-P is not valid for children under the age of 8, but is valid as a parent-report measure of pain and therefore parents and caregivers of these children in this study will instead score their child’s pain level [22]. The FLACC scale is a valid and reliable behavioural observer-report (nurse or health professional) measure of a child’s pain. Self-reports of pain intensity can be difficult to ascertain and inaccurate when a child is receiving sedative and analgesic medications or is too young to verbalise their pain level; therefore the use of the FLACC scale can be a suitable and accurate alternative [23].

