### Statistics

#### Sample size

The primary outcome measure will be days until wound re-epithelialisation. Previous data in paediatric burn patients demonstrated re-epithelialisation within 15 (SD = 4) days and a minimally clinically important difference is 3 days [6]. Thus sample size was calculated at 28 per group at 80% power with an α of 0.05. Allowing for 20% loss to follow-up, a total of 100 participants will be required. The burn centre treats 800 children per year with burns so recruitment for this study should be achievable within 1 year. This sample size will also be adequate to find a significant difference in data collected from pain scores, powered on data from a previous study [6].

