#### Data analysis

All statistical analyses will be conducted using SPSS 21 (IBM Corp., Armonk, NY, USA). Generalised linear models, estimating variance appropriately for repeated measures, will be used to determine whether there are differences among the Acticoat™ group, the Acticoat™ combined with Mepitel™ group and the Mepilex Ag™ group in primary and secondary outcomes. Changes in the intervention effects will be examined with burn depth, burn total body surface area, mechanism of injury, anatomical location of the burn, skin type, ease of dressing removal and application and physical function considered a priori to be of potential interest. All data will be analysed as intention to treat and on a per protocol basis, with the intention to treat analysis being the primary approach for this trial. Any missing data will be handled using the multiple imputation method. All tests will be two-tailed and only those with a *p* value <0.05 will be considered statistically significant.

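### Pain is read until the wound heals, so the number and timing of readings depend on the dressing; the pain models should fix a comparison at the first dressing change, a change-number term and baseline adjustment

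*Protocol article*

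**What the plan says.** All references are to the protocol article.

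- **Reading schedule.** The abstract (Methods/Design) says: "Primary measures of pain, distress and healing will be repeated at each dressing change until complete wound re-epithelialisation occurs", or until grafting. Pain stands under Primary outcome measures. On its four measures (FPS-R, VAS-P, FLACC, and pulse and respiratory rates) the Pain section says: "All four of these measures will be taken before and after dressing removal and before and after dressing application". On timing, the Data collection section says: "All participants in the study will have their dressings changed every 3–4 days at our burn centre as a standard measure". Under Exclusion criteria and Discontinuation/adverse events readings also end at infection or a switch of dressing.
- **Expected effect.** The Study design section hypothesises that a silicone interface shortens healing and also lowers pain.
- **Baseline.** The Recruitment section says: "Baseline measures (pain and behavioural scores from child, nurse and parent, pulse rate and respiratory rate) will be recorded". This is done both before and after the first study dressing goes on.
- **Analysis.** The Data analysis section says: "Generalised linear models, estimating variance appropriately for repeated measures, will be used to determine whether there are differences among" the three arms. Its list of variables (burn depth, burn size, mechanism and others) is introduced for changes in the intervention effect. Neither pain at baseline nor dressing-change number is in that list, and no main pain time point is given.

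**The concern.** How long a child contributes pain scores is decided by healing, which is itself a primary outcome and is expected to differ by arm. Two things follow.

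First, the slower-healing arm supplies a larger share of late readings. If pain eases over successive changes, an average over all readings is pulled down in that arm, and the dressing that heals more slowly can appear gentler. Repeated-measures variance estimation gets the standard error right for correlated readings but does not correct this imbalance in timing.

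Second, the children still attending late changes are selected by healing. A comparison at those changes is no longer between the randomised groups.

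A separate and smaller matter is precision. A pain score taken before the first study dressing is already collected, and nothing says it will be used.

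**Working it through.** **The plan's own figure.** The Sample size section gives a mean of 15 days, SD 4, difference 3 days, two-sided α 0.05 and 80% power. n = 2 × (1.96 + 0.84)² × 4² / 3² = 27.9, so 28 per group, as stated. This concerns healing. For pain the document gives no SD, difference, trajectory or correlation, so the pain inputs below are assumptions.

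**1. Readings per child.** Take healing time T as normal with SD 4 and mean 15 or 18 days (the plan's mean, and that mean plus its 3-day difference). Take a change every 3.5 days, the middle of the plan's interval. A child reaches change k if T > 3.5(k − 1), and the mean number of changes is the sum of P(reach k) over k.

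- Mean 15 days: 4.8 changes.
- Mean 18 days: 5.6 changes.
- Reaching the sixth change (T > 17.5): 1 − Φ(0.625) = 27% against 1 − Φ(−0.125) = 55%.

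**2. Pooled pain with no true difference.** Let pain at change k be 5 − b(k − 1) in both arms, with b the assumed fall per change. The mean over all readings is 5 − b × m, where m = Σ(k − 1)P(reach k) / ΣP(reach k). This gives m = 2.04 for the 15-day arm and 2.44 for the 18-day arm.

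| Fall per change (assumed) | 15-day arm | 18-day arm | Spurious difference |
|---|---|---|---|
| 0 | 5.00 | 5.00 | 0 |
| 0.3 | 4.39 | 4.27 | 0.12 |
| 0.6 | 3.78 | 3.53 | about 0.25 |
| 0.9 | 3.17 | 2.80 | 0.37 |

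At the ends of the plan's interval, m is 2.42 and 2.89 (3 days) or 1.75 and 2.11 (4 days). For falls of 0.3 to 0.9 the difference is then about 0.14 to 0.43, or 0.11 to 0.32.

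**3. What removes it.** GEE models with exchangeable correlation were simulated: 28 per arm, 400 runs, healing at 12 v 15 days, pain SD 2.5, within-child correlation 0.5, no true pain effect. Differences are faster minus slower arm; Monte Carlo error is about 0.025.

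| Fall per change | No change-number term | With change number |
|---|---|---|
| 0 | −0.02 | −0.02 |
| 0.3 | 0.08 | −0.04 |
| 0.6 | 0.25 | 0.01 |
| 1.0 | 0.44 | 0.02 |

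These runs take a child's pain level to be unrelated to healing time. One run at a fall of 0.6, in which children with more pain also healed later, gave 0.30 without the term, 0.06 with it, and 0.02 for the first change alone. The 0.06 is about twice its simulation error. So the term removes most of the distortion, and selection may leave a small remainder at later changes.

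**4. Baseline score.** For a single visit, adjustment multiplies the variance by 1 − r². At r = 0.3 this is 0.91 (9% saved); at r = 0.5 it is 0.75 (25% saved). In the simulation, adding baseline to the model with change number cut the standard error from about 0.51 to 0.41. It did not move the estimate by more than simulation error.

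**The case against.** **The plan does not say it will pool.** A reader might infer that readings are averaged without a time term and that baseline is left out. The document says neither. The variable list concerns effect modification, so a variable's absence from it shows nothing about the main model, and a condensed article may leave model terms to a fuller plan. This stands, and is why the conclusion is conditional. What the document does fix is a reading schedule that ends at a primary outcome expected to differ by arm, with only the variance addressed.

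**Omitted baseline does not bias a randomised comparison.** This stands in full. Baseline is a matter of precision only.

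**The size rests on assumed slopes.** This also stands. The error is zero if pain is flat, would reverse if pain rose over changes, and at 0.12 to 0.37 is about a quarter to three quarters of a standard error of about 0.5.

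**The first change is not perfect either.** The plan allows 20% loss to follow-up, and infection or a switch of dressing ends data collection, so some children may give no score there. It is still the point least affected by healing. Pain over the whole course is also part of the trial's question, so demoting later changes is a trade-off.

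**Scales and power.** The Sample size section claims: "This sample size will also be adequate to find a significant difference in data collected from pain scores". Since FPS-R is collected only "if participant is aged 3 years or over", a reader might infer that the claim fails. The documents do not support that. The sentence does not name FPS-R, FLACC has no age limit, and VAS-P comes from the parent or from the child aged 8 or over. No pain effect size or age mix is given from which to calculate power.

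**Conclusion.** The point holds in a limited form. The number and timing of pain readings depend on healing, and the stated analysis fixes neither a pain time point nor a change-number term. If change number is not modelled and pain falls by 0.3 to 0.9 points per change, an arm healing 3 days later looks less painful by about 0.1 to 0.4 points with no true effect. That range depends on the assumed falls, on normal healing times with SD 4, and on the plan's change interval. It would be wrong to conclude that the pain comparison is biased as planned: the model may contain the term, and pain may be flat. Leaving out the baseline score is a separate loss, about 9 to 25% of single-visit variance at an assumed correlation of 0.3 to 0.5. The effect is modest, but the remedy is nearly free and pain is a primary measure, so the change is worth making.

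**What to change.** In the Data analysis section, state for the pain models that:

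1. the score recorded before the first study dressing is applied is a covariate. The score taken after application must not serve as baseline, because it follows randomisation and may already reflect the dressing;
2. dressing-change number, fitted as a category, and its interaction with arm are included;
3. the main pain comparison is the arm contrast after dressing removal at the first change;
4. later changes are reported by change number as supportive, because the children remaining are selected by healing.

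**Cost.** This is wording only; every item is already collected. The downside is that the headline contrast uses one change rather than about five. In the simulation the first-change standard error was about 0.65, or about 0.59 with baseline, against about 0.41 for all changes with change number and baseline. Baseline adjustment therefore recovers only part of the loss. If the investigators prefer the course of pain as the main question, a model over all changes with change number and baseline keeps that precision, at the price of some selection by healing at later changes.

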**Discussion:**

The results of this study will determine the effects of three commonly used silver and silicone burn dressing combinations on the rate of wound re-epithelialisation and pain experienced during dressing procedures in acute, paediatric partial thickness burn injuries.

**Trial registration:**

Australian New Zealand Clinical Trials Registry ACTRN12613000105741

## Background

The ultimate goal of burn wound healing is to promote early closure as this has considerable influence on the long-term quality and appearance of a hypertrophic scar. It has been demonstrated that even scars considered small in size can contribute to negative psychosocial outcomes for children, hence the importance of effective wound healing techniques [1,2]. The relationship between scar formation and time taken to re-epithelialise in children is well understood by burn clinicians. According to Cubison and colleagues [3], partial thickness burns that re-epithelialise within the optimal time period of 10–14 days generally do so without scarring, and those taking more than 3 weeks will invariably scar. Burns re-epithelialising at between 2 and 3 weeks will have variable amounts of scar tissue laid down depending on many factors including skin type, anatomical location of the burn and age of the child [3].

Children whose burn wounds re-epithelialise at more than 3 weeks post-injury are at a high risk of residual or hypertrophic scarring [3]. Scar management therapy facilitated by occupational therapists to manage and prevent hypertrophic scarring currently involves the use of various types of silicone contact media, pressure garments and splints. Engagement in scar management therapy typically occurs for 18 months or until scars reach maturity. While these scar management techniques are successful for some children in managing scars, there are inevitably children who require ongoing treatment of their scar tissue as they grow older. Scars generally do not grow with the child, and if situated around a joint, can lead to joint contracture and loss of function, resulting in ongoing scar reconstruction to keep up with the child’s growing body [4]. Therefore the initial care of the burn wound and choice of burn dressing are vital in creating the ideal healing environment to ensure rapid re-epithelialisation of the wound and to avoid the possibility of hypertrophic scarring.

In the past 30–40 years, children with burns were treated with daily baths, dressing changes and antiseptic or topical silver sulfadiazine-based creams; however even with appropriate pain relief these procedures were often very distressing and painful for children [5]. It has been well documented that burn wound care procedures are highly traumatic for children and the resultant stress has been shown to interrupt and delay the cascade of wound healing [6]. Decreasing the pain and distress experienced during a dressing change procedure can have positive implications psychosocially for the child as well as encouraging re-epithelialisation of the wound within the optimal healing timeframe [7]. Therefore in the paediatric population, careful attention also needs to be made concerning choosing a dressing that can be applied and removed with minimal pain and stress to the child. A dressing that requires infrequent reapplication also has obvious benefits by decreasing the number of dressing change procedures the child has to undergo.

Small to medium-sized partial thickness burns are mainly managed in the outpatient setting using specialised dressings that promote moist wound healing and prevent wound infection [8]. Unfortunately the antibacterial agents in burn dressings are also cytotoxic to keratinocytes; therefore a fine balance is required between the prevention of a wound infection and the promotion of wound healing [9]. Despite the known cytotoxic effects of antibacterial dressings, they help prevent not only infections (which can delay the rate of re-epithelialisation) but also the possibility of toxic shock syndrome (TSS), which is most likely to occur in the first 3 days post-burn injury and if left untreated can be fatal [10-12].

The standard of care in burn dressings for small to medium partial thickness burns has changed in the last 10–15 years. Currently silver-depositing fabric and foam dressings are the gold standard used to manage the bio-burden of a wound, with or without a silicone skin interface [13]. Acticoat™ (Smith & Nephew, Hull, UK) has been available since the 1990s and is the most widely used silver dressing in the developed world. It needs to be moistened with sterile water to promote the release of silver onto the burn wound and can be left on for 3–4 days. Acticoat™ may be used alone or in combination with a Mepitel™ dressing (Mölnlycke Healthcare, Mikkeli, Finland), which acts as a non-stick interface between Acticoat™ and the burn wound. Mepitel™ is a silicone-coated nylon grid product that utilises non-stick Safetac™ technology to reduce the pain and trauma experienced by children during dressing changes and the amount of silver in direct contact with the wound. Mepilex Ag™ (Mölnlycke Healthcare, Mikkeli, Finland) has been available since 2007 and is a soft foam, silver-impregnated dressing that absorbs exudate and maintains a moist wound environment [14]. Silver particles are released from Mepilex Ag™ when it is moistened from direct contact with wound exudate. It also has a silicone Safetac™ interface layer incorporated within its design that, in a similar way to the Mepitel™, serves to promote easy removal of the dressing and reduce pain and trauma during dressing changes [14].

Many trials have been conducted regarding the efficacy of silver dressings for treating burn injuries, using topical silver sulfadiazine applications as the control or comparator dressing. However, these silver sulfadiazine applications have been shown to delay re-epithelialisation and are painful to apply and remove, indicating the possibility of bias in the results of these trials [13,15,16]. Additionally, despite the large number of silver-impregnated burn dressings that have become available on the market, very few high-level trials have been conducted that compare these dressings in paediatric or adult patients. For paediatric patients in particular, identifying silver dressings that are associated with lower levels of pain, require fewer reapplications and promote a fast rate of re-epithelialisation is vital.

The aim of this study is to then determine whether one of three silver- and silicone-containing burn dressings—Acticoat™, Acticoat™ combined with Mepitel™ or Mepilex Ag™—will be more effective in terms of pain experienced and the rate of re-epithelialisation of acute, partial thickness burns in children.

The following protocol for this study has been reported as per CONSORT guidelines [17].

